## Abstract

**Background:**

Clinical data show that due to the limited effects of lifestyle regulation and unsatisfactory drug adherence, only half of the hypertensive population have their blood pressure (BP) under control. In recent years, catheter-based renal denervation (RDN) has been used as a novel approach for treating uncontrolled hypertension. The safety and efficacy of catheter-based RDN have been confirmed by a number of studies and trials in which the participants were all non-Chinese and RDN was conducted via radiofrequency or ultrasound.

**Methods/design:**

This study is a prospective multicenter randomized sham-controlled trial that aims to investigate the safety and efficacy of cryoablation RDN (cryo-RDN) using a novel dedicated cryoablation balloon catheter (Cryofocus, China). A total of 200 Chinese patients who have uncontrolled hypertension despite standard medical treatment will be enrolled. With drug standardization, eligible participants will be randomized in a 1:1 ratio to undergo cryo-RDN treatment or renal angiography alone as a sham treatment.

The primary endpoint is defined as the change in 24-h ambulatory systolic blood pressure from baseline to 6 months. Office BP and other 24-h ambulatory BP are included as secondary endpoints. Safety endpoints primarily include any adverse effects.

**Discussion:**

This study was designed to verify the safety and efficacy of cryo-RDN with Cryofocus balloon catheters in uncontrolled hypertensive patients on polypharmacy. The aim is to provide a new way to improve the control of hypertension in China as a complement to drug therapy.

**Trial registration:**

ChiCTR, ChiCTR1800017707. Registered on 10 August 2018.

**Electronic supplementary material:**

The online version of this article (10.1186/s13063-019-3693-9) contains supplementary material, which is available to authorized users.

## Background

Globally, hypertension is a chronic disease and a leading risk factor for cardio- and cerebrovascular comorbidities, resulting in high mortality and economic burden [1, 2]. However, despite adequate pharmacological (drug combinations) and lifestyle changes, approximately 50% of the hypertensive population have suboptimal control of their blood pressure (BP) [3].

In 2009, Krum et al. provided the first report showing that renal denervation (RDN) was suitable for treating resistant hypertension [4]. In the last decade, there have been numerous RDN studies conducted with different designs [5, 6]. Although study outcomes vary, the safety of RDN in lowering BP is clear, but its efficacy was uncertain. However, after the positive results of the latest HTN MED-OFF trial, the efficacy of catheter-based RDN therapy is now well accepted [7].

Most RDN studies use a radiofrequency current and ultrasound as the energy sources for ablating the renal sympathetic nerves. In 2014, Prochnau et al. reported an ideal BP decline in 10 patients following cryoablation after a failed attempt at radiofrequency RDN [3]. Contrast agent in the balloon forms an ice ball, absorbing heat spherically from surrounding tissue.The overall freezing and rewarming procedure is much shorter than that for other denervation devices. Our previous animal study and the first-in-man study show that cryoablation RDN (cryo-RDN) is efficient and safe. There were no vascular events relating to BP reduction [8].

In China, although approximately half of adults between the ages of 35 and 75 years have hypertension, many of these individuals have poorly controlled BP, with control rates and treatment control rates of 13.8% and 41.1%, respectively [9, 10]. To explore the safety and feasibility of cryo-RDN in Chinese patients with uncontrolled hypertension further, we have developed a rationale and methodology for a prospective multicenter randomized sham-controlled trial using a 7.5F cryoablation catheter from the Cryofocus system. Figure 1 is the schedule of enrolment, interventions, and assessments for the trial.

**Fig. 1 Fig1:**
[figure not shown]
Schedule of enrolment, interventions, and assessments. Blood pressure monitor, cryo-RDN cryoablation renal denervation

## Methods/design

### Study design

Our trial is a prospective multicentered single-blinded randomized sham-controlled trial to evaluate the efficiency in BP reduction and safety in Chinese patients with uncontrolled hypertension compared with the sham arm. It uses a Cryofocus RDN device. The study will be conducted in accordance with the principles of the Declaration of Helsinki in 13 medical centers nationwide. Each patient will be screened twice before receiving the cryo-RDN, if applicable. A brief flow chart (Fig. 2) is listed below.

**Fig. 2 Fig2:**
[figure not shown]
Screening flow chart. 4w 4 weeks, cryo-RDN cryoablation renal denervation

### Study patients

In total, 200 patients with uncontrolled hypertension despite receiving pharmacological therapy from 13 clinical centers in China will be enrolled. The definition of uncontrolled hypertension is given in Inclusion criteria at the first screening visit section. At the first visit, patients will be screened for eligibility. After being fully informed about the study and all risk factors, patients will be asked to sign the informed consent form. They will then be prescribed the standardized medications for no less than 4 weeks as a run-in period. At the second enrollment screening visit, patients who meet the additional inclusion criteria will undergo an additional preintervention examination. Parameters at the second screeing visit will be set as baseline and the intervention has to be performed within 2 week.

#### Inclusion criteria at the first screening visit

Patients must meet all the following criteria:
Patient is ≥18 and <75 years old at the time of randomization.Patient has continually taken antihypertensive drugs ≥3 months.Patient agrees to cooperate with all study procedures.Patient provides written informed consent to participate in this clinical study.

In addition, the patient must meet one of the following conditions:
Patient is currently on two or three types of antihypertensive drugs with 150 mmHg ≤ office SBP ≤ 180 mmHg and office DBP ≥90 mmHg.Patient is currently on four types of antihypertensive drugs with office SBP ≥140 mmHg and office DBP ≥ 90 mmHg.Patient has been on five types of antihypertensive drugs for ≥3 months, and office SBP ≥140 mmHg, office DBP ≥ 90 mmHg, and 24-h SBP ≥135 mmHg.

#### Exclusion criteria at the first screening visit

Patients will be excluded if they meet any of the following criteria:
Patient is diagnosed with secondary hypertension.Patient has a history of renal artery interventional therapy, for example, stents.Patietnts has renal artery disease or the presence of morphology variation (including but not limited to aneurysm, stenosis, severe calcification of the renal artery, dissection, and multiple renal arteries).Patient had a myocardial infarction, unstable angina pectoris, syncope or a cerebrovascular accident within 6 months prior to screeningPatient has widespread atherosclerosis with recorded intravascular thrombosis.Patient has heart valve disease with significant hemodynamic changes.Patient has uncontrolled pulmonary hypertension.Patient has an estimated glomerular filtration rate of less than 60 mL/min/1.73 m2 according to the Modification of Diet in Renal Disease formula.Patient has a tendency for significant bleeding or blood system disease (platelet count <50 × 10^9^/L or INR>1.5).Patient has an implantable cardioverter defibrillator or a pacemaker.Patient has a severe or systemic infection.Patient has type 1 diabetes mellitus.Patient has a condition, except sleep apnea hypopnea syndrome, that requires long-term oxygen inhalation or mechanical ventilation.Patient is allergic to the contrast.Patient is pregnant, breastfeeding, or preparing for pregnancy.Patient is addicted to alcohol or other drugs.Patient has been diagnosed with a mental illness.Patient has any other disease that may have an adverse effect on their safety in the context of the trial.Patient has been enrolled in any other clinical trial of a drug or device within 6 months prior to enrollment.Patient has any other condition that makes their participation inappropriate, at the investigator’s discretion.

#### Inclusion criteria at the second screening visit

The participant must meet one of the following conditions:
150 mmHg ≤ office SBP < 180 mmHg, office DBP ≥90 mmHg, and 140 mmHg ≤ 24-h SBP < 170 mmHg: Patient is suitable for two or three types of drugs. They will be instructed to take the standardized pharmacological therapy for at least 4 weeks (Additional file 1 and Additional file 2: Table S1).Office SBP ≥140 mmHg, office DBP ≥90 mmHg, and 24-h SBP ≥135 mmHg: Patient is suitable for four types of drugs. They will be instructed to take the standardized pharmacological therapy for at least 4 weeks.Patient is currently on five types of antihypertensive drugs: They will continue to use these drugs until the end of follow-up.

#### Withdrawal

Patients may be withdrawn from the study for any of the following reasons:
They may choose to withdraw for any reason.They have severe side effects that require the use of test product to be stopped during the intervention.Based on the investigator’s discretion, the patient is no longer eligible for the study for any reason.Any other rational reason to withdraw them.

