### Interventions

Eligible patients will undergo either cryo-RDN with Cryofocus system or dual renal angiography only. It is expected that their previously prescribed standardized antihypertensive drugs will remain unchanged in the 6-month follow-up period after the intervention.

However, if in the first 3 months after the intervention a patient experiences dizziness, fatigue, or other symptoms of hypotension, or after 4–6 months the patient has office SBP < 100 mmHg and office DBP<50 mmHg, then the investigators can decrease the number or the dosage of the antihypertensive drugs. Moreover, additional drugs can be added at 4–6 months if a patient taking two or three types of standard antihypertensive drugs has office BP>160/110 mmHg or if a patient taking four types of standard antihypertensive drugs has office BP > 180/110 mmHg (the rules for adjusting dosages are listed in Additional file 2: Table S2).

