### Cryo-RDN procedure

Angiography and cryo-RDN procedures will be performed through the femoral artery by one or two designated interventionists at each study site after a combined training session. Under general anesthesia, a 10F sheath and a 6F Judkins Right (JR4.0) catheter will be inserted through femoral access into the renal arteries, and angiography will be performed on dual renal arteries to confirm anatomic feasibility and ablation sites. Intraprocedural anticoagulation will be administered with 100 units of heparin per kg. After randomization based on computer-generated random numbers, patients in the sham arm will be maintained under anesthesia for another 30 min. For patients in the cryo-RDN arm, the 6F catheter will be removed and, according to angiography, properly sized cryoablation balloons will be advanced to the distal segment of the main renal artery through an 8F guidance catheter and a 0.018″ SV-5 guide wire (Cordis, Johnson & Johnson, North West, Florida, USA). During the cryoablation procedure, the regional renal blood flow will be blocked for approximately 5 min on each side with cooling (average −95 °C, ranging between –115 and –80 °C) and rewarming. If needed, the cryoablation balloon catheter will be withdrawn and placed in a catheter of the right size for ablation on the other side of the renal artery. In addition, a bifurcation with a diameter ≥3.0 mm will also be additionally ablated, as a recent expert consensus suggests that this gives better clinical outcomes [7]. A final renal angiography will check that there is no renal artery obstruction, perforation, or dissection. The delivery system and sheath will be removed. Hemostasis of the femoral access site will be achieved using standard techniques.

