### Outcome measures

The primary outcome of this study is the difference in the change in 24-h SBP from baseline to 6 months between the cryo-RDN treatment arm and the sham treatment arm. At each participating site, one or two staff members from the laboratory department, and not the clinical department, will be allocated to undertake the 24-h BP measurements during the study period.

The secondary outcomes are as follows:
Difference in change in 24-h SBP (daytime and nighttime) from baseline to 6 months between the cryo-RDN treatment arm and the sham treatment armDifference in change in 24-h SBP (daytime, nighttime, and 24-h) from baseline to 6 months between the cryo-RDN treatment arm and the sham treatment armDifference in change in office BP (SBP and DBP) from baseline to 6 months between the cryo-RDN treatment arm and the sham treatment armCharacteristics of patients who required an adjustment to their medication after the interventionAdherence of patients to taking their antihypertensive drug based on the eight-item Morisky Medication Adherence ScaleOperational performance evaluation of the test device in the cryo-RDN treatment armSide effects possibly caused by the test deviceMajor adverse eventsOther adverse events

Safety endpoints primarily include any adverse incidents, including but not limited to puncture-related vascular injury, renal artery complications, renal complications, systematic reactions and a change in renal function, which may be caused by the test device or other factors.

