### Statistical analysis

The statistical analysis plan will be developed and performed by independent statisticians from the data monitoring committee. SAS software V.9.4 (SAS Institute, Cary, NC) will be used for the statistical analysis. Based on the intention-to-treat principle, the full analysis set and per protocol set will be adopted as the primary analysis populations. A two-sided *p* < 0.05 will indicate significance in all statistical tests. Appropriate descriptive indicators and hypothesis testing methods will be selected cautiously. Data, including demographics, baseline characteristics, and safety, will be summarized by treatment arm.

The primary efficiency outcomes are powered by a superiority test to detect the change in 24-h SBP from baseline to 6 months after the intervention. The sensitivity analysis will have a stratifying variable center as a fixed effect of an analysis of covariance (ANCOVA). A BP reduction will be tested by paired *t*-tests with 95% confidence intervals for the differences between treatment arms. Other categorical data will be tested using either Pearson’s χ^2^ test or Fisher’s exact test. Rank data will be tested by either the Wilcoxon rank sum test or the Cochran–Mantel–Haenszel test. Mixed-model repeated measures analysis including terms for the baseline measurement, types of drugs taken, and medication adjustments during the follow-up will be used for the reduction in BP.

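### The withdrawal rule lets patients leave the study when severe side effects stop the device, a post-randomisation exit open to the cryo-RDN arm only that can cost late safety and 6-month BP data

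*Protocol article*

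**What the plan says.** The Withdrawal section opens with "Patients may be withdrawn from the study for any of the following reasons". Two of its four reasons matter here. One is "They have severe side effects that require the use of test product to be stopped during the intervention". The other lets the investigator judge that "the patient is no longer eligible for the study for any reason". The remaining two are the patient's own choice and an open clause for any other rational reason. The object of withdrawal is the study. The section does not distinguish stopping the device from ending follow-up.

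The Interventions section defines the arms: "Eligible patients will undergo either cryo-RDN with Cryofocus system or dual renal angiography only". The Cryo-RDN procedure section gives the order of events. Diagnostic angiography comes first, then allocation ("After randomization based on computer-generated random numbers, patients in the sham arm will be maintained under anesthesia for another 30 min"), and only then is a balloon advanced in the cryo-RDN arm.

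The Statistical analysis section states: "Based on the intention-to-treat principle, the full analysis set and per protocol set will be adopted as the primary analysis populations". The Outcome measures section says: "Safety endpoints primarily include any adverse incidents, including but not limited to puncture-related vascular injury, renal artery complications, renal complications". It also covers change in renal function. The Study visits section schedules visits before discharge and at 1, 3 and 6 months, with a second renal angiography at 6 months.

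**The concern.** A patient whose cryoablation is stopped for a severe side effect has already been randomised. If that patient then leaves the study, the 6-month primary measurement and all later safety assessments are never made. No sham patient can leave by this route, because no sham patient receives the test product. The loss is therefore related both to arm and to outcome, which is the kind of loss that an intention-to-treat analysis is meant to avoid.

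Safety is the main stake. The trial sets out to verify the safety of a new device, and patients with a severe reaction during ablation are those in whom the later state of the renal artery and renal function is most informative. For efficacy, these patients had incomplete treatment, so removing them moves the comparison towards those in whom the procedure went well.

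The discretion clauses add a lesser risk. They cover both arms, but they can be used after randomisation. The Study design section calls the trial single-blinded, so the person exercising discretion may know the allocation.

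**Working it through.** **Step 1. When the exit can occur, and in which arm.** By the Cryo-RDN procedure section, the order is angiography, randomisation, then the balloon. A stop of the test product during the intervention must therefore follow randomisation. By the Interventions section, the sham arm has angiography only. The reason can arise in the cryo-RDN arm alone.

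**Step 2. What is kept and what can be lost.**

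| Item | Status if the patient is withdrawn |
|---|---|
| The acute severe side effect | Kept: it occurs in the trial and falls under the safety endpoints in Outcome measures |
| Adverse events after withdrawal | Can be lost |
| Renal function at later visits | Can be lost |
| Renal angiography at 6 months | Can be lost |
| 24-h SBP at 6 months (primary) | Can be lost |

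**Step 3. Size of the efficacy distortion.** Inputs from the Sample size calculation section: difference 8 mmHg, SD 18 mmHg, 100 patients per arm. Assumptions, because the article gives no figures: x of 100 cryo-RDN patients are stopped (x = 1, 2, 5, 10); these patients gain 0 mmHg over sham and all others gain 8; withdrawn patients are left out of the comparison; SD stays at 18; nobody else is lost.

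- Effect with everyone kept: (1 − x/100) × 8
- Effect with stopped patients removed: 8
- Overstatement: 8x/100
- Standard error, all kept: 18 × √(1/100 + 1/100) = 2.546 mmHg
- Standard error, stopped patients removed: 18 × √(1/(100 − x) + 1/100)
- Power: Φ(effect/SE − 1.96)

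| x | Effect, kept | Overstatement | Overstatement ÷ 2.546 | Power, kept | Power, removed |
|---|---|---|---|---|---|
| 1 | 7.92 | 0.08 | 0.03 | 87.5% | 88.0% |
| 2 | 7.84 | 0.16 | 0.06 | 86.9% | 87.8% |
| 5 | 7.60 | 0.40 | 0.16 | 84.7% | 87.3% |
| 10 | 7.20 | 0.80 | 0.31 | 80.7% | 86.4% |

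Even at x = 10 the overstatement is about a third of a standard error.

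**Step 4. The plan's own figures.** The article gives no figure for stopped procedures or for withdrawals by this route, so there is none to reproduce on this point. The stated 81 per arm at 95% power does not reproduce from 8 mmHg and SD 18: 2 × (18/8)² × (1.960 + 1.645)² rounds up to 132 per arm, and 81 per arm gives 80.7%. That is a separate matter. The overstatement in Step 3 does not depend on it, since 8x/100 contains no sample size.

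**The case against.** The strongest reply has five parts.

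*The harm is still counted.* This stands. The triggering event happens while the patient is in the trial, and Outcome measures includes any adverse incident, side effects possibly caused by the device, and its operational performance. A reader might infer that device harms vanish from the cryo-RDN arm, for instance by setting 0 of 95 against 5 of 100 events. The document does not support that: the comparison mixes later events with acute ones, and the acute ones remain reportable.

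*Failed procedures are not named.* This also stands. The clause covers severe side effects only. A technical failure without harm could lead to withdrawal only under the general clauses, which apply to both arms. It does not follow that failures as such leave one arm only.

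*The wording is permissive, and leaving follow-up is not exclusion from analysis.* True as far as it goes. The clause says that patients may be withdrawn, and nothing says that they leave the full analysis set. How missing values are handled is properly left to the analysis plan. But no analysis plan can recover a 6-month reading or angiogram that was never taken; it can only replace it by assumption, and for this exit in one arm only. The per protocol set is also named as a primary population.

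*The article is condensed.* A full protocol may well provide for follow-up after withdrawal. The point here is the rule that the article states, which makes the study the thing left.

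*Discretion clauses are usual and cover both arms.* Accepted. Whether follow-up investigators know the allocation is not stated, and 24-h BP is measured by laboratory staff outside the clinical department. This supports only a secondary concern.

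**Conclusion.** The point holds in a limited form. The Withdrawal section permits an exit from the study that follows randomisation, can arise only in the cryo-RDN arm and is triggered by a severe device-related outcome. This is at odds with the stated intention-to-treat principle. The exit is permitted and not required, so the loss is a risk and not a certainty.

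The larger consequence is missing late safety information in a small but important group. It cannot be quantified from the document. The efficacy consequence is likely small: 0.08 to 0.80 mmHg on an assumed 8 mmHg effect. That range rests on an assumed 1 to 10% of stopped procedures, no benefit in those patients and their exclusion from the comparison.

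A reader might go further and conclude that the device will look both safer and more effective than it is. The document does not support that, given that acute events are reported and the possible efficacy shift is small. The change is still worth making, because the lost measurements cannot be recovered afterwards.

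**What to change.** Reword the Withdrawal section so that stopping the device and leaving the study are two different things. For example:

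> If use of the test product is stopped during the procedure, or an investigator judges after randomisation that a patient is no longer eligible, the patient remains in the study. Scheduled follow-up continues to 6 months (24-h BP, renal angiography, renal function, adverse events) as far as the patient consents. The patient stays in the full analysis set and the safety set as randomised.

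Also report, by arm, the number of stopped procedures, the reason, and how many of these patients have each 6-month assessment.

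The criteria for stopping treatment are untouched. Whether an individual can undergo a given assessment remains a matter of consent and clinical judgement; a patient who declines the angiography can still contribute BP and adverse event data.

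The cost is an amended paragraph and visits already scheduled, for a few patients. The 3- and 6-month visits involve hospital admission, so the cost is not nil. The Trial status section says that recruitment had not begun at submission, so at that stage the wording could be changed before any patient was affected.
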